### Procedure

#### Flowchart for subprojects

There are two subprojects, one on grammar learning and one on word learning. Each will randomly recruit 180 participants. Both projects will implement the same test battery and MRI sequences, but will differ on the fMRI paradigm and the corresponding training sessions (i.e., session 2 and home-training; see Fig. 1 and Table 1). Each fMRI paradigm is specifically developed to measure the neural correlates necessary for either L2 word learning (i.e., Finnish), L2 grammar learning (i.e., Icelandic), or L2 knowledge acquisition (i.e., artificial language task). All fMRI paradigms, as well as the rest of the protocol, are developed and tested with several pilot studies to ensure high-quality data can be collected for both young and adult participants.

**Fig. 1 Fig1:**
[figure not shown]
Study flowchart for each subproject: word project (dark blue arrow), grammar (light blue arrow). Each subproject will include a sample of 180 participants between the ages 8 and 25 years. All 4 sessions, except the home training, will take place at the Donders Institute. In the word project (dark blue arrows), following the test battery during session 1, participants will return to the Donders Institute to learn the first half of the Finnish words and to become familiarized with the fMRI tasks in a mock scanner. During session 3, participants will begin by learning the second half of the Finnish words, outside the MRI scanner. Once the learning tasks have been completed, participants will perform the 4AFC test while in the MR scanner. Once outside the scanner, participants will perform the Cued Recall task. Finally, in session 4, participants will be familiarized with the artificial language learning task in the mock scanner, and then proceed to perform the artificial language learning task in the MR scanner. In the grammar project (light blue arrows), participants will receive the test battery and a short Icelandic word training during session 1. In the following session, participants will undergo a short grammar training, with half of the learned words, to familiarize themselves with the Icelandic grammar rules before they will perform the grammar judgment task in the MRI scanner. After this session, participants will undergo a 5-day training, ~ 30 min each day, to learn the Icelandic grammar rules further as well as some additional Iceland words that will not be used in the grammar training. Finally, in the last session, participants will complete the second grammar judgment task on the grammar trained and untrained Icelandic words. Besides the task-based fMRI data, additional MR data will be collected during both MRI sessions

**Table 1 Tab1:** Study procedure chart for test battery and MRI protocol

Test battery	MRI protocol
**Cognitive tasks**	**1st MRI session**
*Matrix reasoning*	*MP2RAGE*
*Proficiency test L1 & L2*	Word learning fMRI task^a^
*Grammar test L1 & L2*	Grammar fMRI task: pre^b^
*Fluency test L1 & L2*	*Diffusion weighted imaging*
*ASRT task*	
*Word Pairs*	**2nd MRI session**
*Digit Span*	*MPRAGE*
*Non Word repetition task*	ArtLang fMRI task^a^
*StopIt Task*	Grammar fMRI task: post^b^
*Reading task*	*Resting-state fMRI*
**Questionnaires**	
*Socio-economic status*	
*Puberty development scale*	
*Handedness inventory*	
*Language experience*	

Study procedure chart showing research assessments for the word subproject (^a^), the grammar subproject (^b^), and overlapping—identical—assessments for both subprojects (italic). L1 = native language, L2 = second language, i.e., English

#### Cognitive tests

##### Language proficiency in Dutch and English

Dutch (L1) and English (L2) proficiency will be measured through a variety of standardized tests that measure vocabulary knowledge, grammatical ability, and word production in both languages. Vocabulary proficiency of each participant will be estimated using the standardized Peabody Picture Vocabulary Tests for the Dutch (PPVT-III-NL) and English (PPVT-4) language [127, 128]. Within the PPVT, each trial of the 204 or 228 trials in the Dutch and English versions respectively, presents visually four pictures and aurally one word. Participants have to select the picture that best matches the aurally presented word, which can be a verb, adjective, or noun. Grammar ability will be assessed using the—recently developed—Syntest and the test for reception of grammar (TROG-2) for the Dutch and English language respectively [129, 130]. In each grammar test, participants will match an aurally presented grammatical sentence with one of four presented pictures. The category fluency test and the initial letter fluency test will be employed to estimate the participants’ word production in Dutch and English [131]. For the category fluency test, participants need to generate exemplars from categories for vegetables and professions in Dutch, and animals and fruits in English, within 60 s per category. The initial letter fluency test requires participants to generate words from initial letters (i.e., Dutch: M and S; English: F and A) with a time limit of 60 s per letter.

##### Cognitive memory ability assessments

Several tests will be applied to assess individual variability in three main memory domains, that is, declarative, procedural, and short-term working memory. Declarative memory abilities of all participants will be measured through the word-pairs test from the Dutch version of the Wechsler scale of adult intelligence (WAIS; [129]). Procedural memory abilities will be estimated through an adapted version of the alternating serial reaction time (ASRT) task, where participants implicitly learn a repeated pattern of visual cue appearances that can occur in four different positions [132]. Short-term verbal memory will be assessed with the digit span test and the non-word repetition task (adapted from 134). The digit span test includes the backward, forward, and sorting task from the Wechsler scale of intelligence where adult participants will receive the WAIS-IV-NL and the younger participants until the age of 17 will receive t he WISC-V-NL version [133, 135].

##### General cognitive assessments

Various general cognitive assessments that measure non-verbal intelligence, cognitive control, and reading ability will also be collected. Non-verbal intelligence will be estimated using the matrices subtest from the Wechsler scale of intelligence for adults (WAIS-IV-NL) and children (WISC-V-NL), with the cut-off age of 17 years [133, 135]. To measure cognitive control, a stop-it task will be performed [136]. During this stop-it task, participants need to press either a left or right button when a square or circle is presented. However, this action has to be inhibited when the visual stimulus is accompanied by an auditory cue, that is, a loud beep. Reading ability will be checked using the Dutch standardized 3-min reading test, where participants have to read 120 verbs and nouns aloud within 3 min [137].

#### Questionnaires

Since several environmental and intrinsic factors could influence L2 learning, we will include a number of additional measures. Quantitative data about physical development, social-economic status, handedness, and language experience will be collected through various questionnaires. First, to assess physical pubertal development, all participants under 18 years will be asked to fill out a standardized pubertal development questionnaire, where their bodily maturation will be assessed through five questions with a 5-point Likert scale [138]. Secondly, participants or their caregivers (in case of underage participants) will be given a questionnaire about their income, education, and occupational status, to estimate their socio-economic status. Also, handedness will be measured through a questionnaire, namely through a Dutch version of the Edinburgh Handedness Inventory [139]. In addition to the previously mentioned Dutch and English proficiency tests, we will also ask the participants about their usage and experience with any foreign languages through an extensive language questionnaire.

#### Neuroimaging

All neuroimaging data will be acquired on a 3 T Siemens SKYRA MRI scanner using a 32-channel head coil at the Donders Institute for Brain, Cognition and Behaviour in Nijmegen. To minimize head movements, a small pillow will be placed in the head coil to stabilize the participant’s head and make them lie comfortably. Furthermore, a small skin-friendly tape will be placed on the forehead of each participant and the head coil base to provide them with head motion feedback, which is a child-friendly way to prevent head movement. Before each scan session, participants will be invited to lie in a mock scanner to acclimatize to the MRI scanner and the previously mentioned procedures.

##### Gray matter structural measurements

We will collect two whole-brain T1-weighted images during which participants are asked to lie as still as possible while watching short cartoons. One structural T1-weighted image will be acquired using a Magnetization Prepared Rapid Gradient Echo (MPRAGE) sequence. This sequence will allow for gray-matter density—that is, volume—measurements, but more importantly these images will serve as anatomical reference for co-registration and normalization of all neuroimaging data collected within the study. The parameters for this MPRAGE sequence are as follows: repetition time (TR) = 2000 ms; echo time (TE) = 2.01 ms; matrix size = 256 × 256; field-of-view (FOV) = 256 mm; flip angle = 8°; voxel size = 1 mm; slice thickness = 1 mm, 192 sagittal slices covering the entire brain. Parallel imaging (iPAT = 2) will be used to accelerate the acquisition, resulting in an acquisition time of 4 min and 40 s. The other high resolution T1-weighted image in this protocol is the MP2RAGE, a modified in-ho use M PRAGE sequence, which generates two different images at different inversion times [140]. This sequence is added to examine the properties of the gray matter beyond volume (i.e., surface and thickness) more precisely. The MP2RAGE sequence parameters are as follows: TR/TI1/TI2 = 5000/700/2500 ms; matrix size = 256 × 216; FOV = 256 mm; flip angle1 = 6°; flip angle2 = 5°; voxel size = 1 mm; slice thickness = 1 mm, 224 sagittal slices coveri ng th e entire brain. Parallel imaging (iPAT = 4.6) will be used to accelerate the acquisition, resulting in an acquisition time of 4 min. A corresponding low-resolution B1 fieldmap will be collected subsequently to correct for small inhomogeneities [141]. A total of 42 sagittal slices will be acquired, covering the entire brain in an acquisition time of 20 s. The B1 fieldmap sequence parameters are as follows: TR = 1000 ms; TE = 2.07 ms; matrix size = 256 × 216; F OV = 256 mm; voxel size = 1 mm; slice thickness = 1 mm.

##### White matter structural measurements

To examine white matter structures, we will acquire diffusion-weighted images. This acquisition will consist of a two-shell protocol with gradient directions that were uniformly distributed over the sphere: TR = 2930 ms; TE = 89.6 ms; multiband acceleration factor = 3; FOV = 212 × 212 × 138 mm, 2.0 mm^3^ isotropic voxels; 69 slices; 80 directions with b = 1000, 2000 s/mm^2^ (40 per b-value), and six b = 0 volumes, GRAPPA factor 2, phase partial Fourier Off; and a total acquisition duration 4:53 min. To allow for offline distortion correction of the diffusion-weighted images, 7 more b0 s/mm^2^ volumes will be acquired (duration 1:02 min) using exactly the same sequence parameters except for the inverted k-space read-out trajectory.

##### Resting-state functional MRI measurements

To obtain the resting-state data, a multiband accelerated T2*-weighted EPI sequence will be used with the following parameters: TR = 1000 ms; TE = 35.2 ms; multiband acceleration factor = 6; matrix size = 104 × 104; FOV = 213 mm; flip angle = 60°; voxel size = 2 × 2 mm; slice thickness = 2 mm, 66 axial slices covering the entire cerebrum. The duration of the scan is 8 min and 10 s, in which 480 volumes are obtained. Additionally, fieldmap data (one phase difference image and two magnitude images at two different echo times) will be acquired for distortion correction. Participants will be instructed to relax, lie as still as possible, and remain awake. During the scan, lights will be 50% dimmed and participants can either fixate on a white cross that is presented on a black screen in the scanner, or they can keep their eyes closed.

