## Methods/design

### Participants

#### Sample size and recruitment

This project plans to recruit 360 Dutch native speakers from the ages 8 to 25 years from the general population. We aim to distribute all 360 participants evenly over this age range to have enough power to detect both age-related variability and individual variability. Adults will be partly recruited through a specialized research participation system at the Radboud University, and we will additionally promote our study through posters at university faculties, supermarkets, and social media posts. Young participants and their caregivers will be reached through flyers and posters in their schools, libraries, sport clubs, and community events. Individuals choose to take part in this study voluntarily, so that we will create a self-selecting sample. Data collection has started in 2019 and is projected to end in 2023.

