### Statistical analyses

To examine the neural correlates underlying age-related variability in new word and grammar learning, several analyses will be performed, which can be divided into two stages. The first stage is to estimate the cognitive and neural fingerprints that will be fed into the statistical analyses. For the neural fingerprint of word and grammar learning, the following functional and structural correlates will be estimated for all participants in each subproject: (a) network of functional regions (de)activated during the language fMRI paradigms, (b) functional connectivity nodes and maps, (c) white matter metrics (e.g., diffusion tensor and tractography measures), and (d) gray matter metrics (e.g., cortical thickness, surface area). To estimate the cognitive fingerprint that will serve as the predictor for individual differences in new word and grammar learning, the cognitive and questionnaire measurements will be inputted into principal component analyses to create combined factor scores, such as L1 factors (Dutch proficiency), L2 factors (English proficiency), and language aptitude. In the second stage, with these fingerprints, we will first explore potential age-related effects within each modality using regression analyses where age—as a continuous variable—will be the predictor for the earlier assessed functional and structural metrics. For this, both linear and non-linear effects will be examined by fitting linear and non-linear models using generalized linear models (GLMs) and generalized additive models (GAMs). Next, linked independent component analyses will be used to integrate all imaging modalities. This data-driven approach provides an automatic decomposition of the images into spatial components characterizing the intersubject brain structural variability, i.e., each spatial component represents a mode of variation of brain structure and function across all participants [147]. Post hoc multiple (linear/non-linear) regression analyses will investigate the relationship between the identified spatial components, age and cognitive factors. Lastly, structural equation modeling will be used to investigate which fingerprint features (such as age, cognitive factors, and functional and structural metrics within the identified spatial components) best predict new word or grammar learning success.

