This study employs self-selecting sampling; participants will be voluntarily recruited from the general population t hrough promotion material at schools, libraries, sport clubs, and higher education recruitment systems. Our recruitment strategy could, therefore, lead to a biased sample of high-functioning, high-educated, and motivated participants with a high socioeconomic status (SES). This may limit the generalization of our results to the general population. Interestingly, the literature indicates that SES, motivation, and education level are factors that could influence L2 learning. For this r eason, we have included meas ures for SES, motivation, and education level in our study protocol. Although the chosen cross-sectional study design allows us to investigate age-related differences in a large sample within a short timeframe, it does have one important shortcoming. That is, the direct cause-and-effect of development on L2 learning success is difficult to pin down due to inter-individual variability. To compensate for this, we plan to collect a large sample. Additionally, we will measure and p otentially correct for developmental and environmental factors to reduce inter-individual variability when investigating age-related effects. Another limitation is the multilingual population of the Netherlands. In particular, individuals with a high SES learn multiple languages in high school and use English on a daily basis in higher education. Luckily, however, children in the Netherlands are already exposed to English and other languages at a young age and thus even our youngest participants ar e not monoling ual. But the children still have less L2 exposure than older individuals. This could cause differences in language knowledge between the preadolescents and young adults. To deal with this limitation, our protocol contains an extensive language questionnaire that measures English (and other) language knowledge and exposure, which will be factored into our analyses.

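### Eye state in the resting-state scan is the participant's choice and no stated analysis accounts for it: this adds noise if it affects connectivity, and biases the age effect if the choice also varies with age

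*Protocol article*

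**What the plan says.** The section on resting-state functional MRI measurements gives one general instruction, "Participants will be instructed to relax, lie as still as possible, and remain awake", and then leaves the viewing condition open: participants may "fixate on a white cross that is presented on a black screen in the scanner, or they can keep their eyes closed". The scan lasts just over eight minutes in a half-lit room.

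The Statistical analyses section makes "functional connectivity nodes and maps" one of the four parts of the neural fingerprint. In the second stage, "age—as a continuous variable—will be the predictor for the earlier assessed functional and structural metrics". After that, "linked independent component analyses will be used to integrate all imaging modalities", and the resulting components go into post hoc regressions and a structural equation model.

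The closest the article comes to an adjustment is under Strengths and limitations, where the investigators may "correct for developmental and environmental factors to reduce inter-individual variability when investigating age-related effects". Eye state is not named there or anywhere else in the article.

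On sample size, "We aim to distribute all 360 participants evenly over this age range", which is 8 to 25 years. Each of the two subprojects takes 180 participants, and the resting-state scan is common to both.

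**The concern.** The scan condition is self-selected, and age, the predictor of interest, could plausibly influence the selection. Suppose connectivity differs between open and closed eyes, and older participants choose one state more often than younger ones. A regression of connectivity on age then attributes part of the state difference to maturation. Linked independent component analysis and the structural equation model use the same data, so they would carry the distortion forward.

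The article counts on a large sample to offset variability between individuals. That helps against noise but not against this bias: a fixed spurious slope is declared significant more often as the sample grows.

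If the choice has nothing to do with age, the only cost is extra residual variance in the connectivity measures.

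**Working it through.** The article states no figure on this point, so there is none to reproduce. The calculations below show how large the effect could be.

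**Inputs from the article.** N = 360 in total and 180 per subproject; ages spread evenly over 8 to 25; age analysed as a continuous predictor.

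**Assumptions (not in the article).** State effect d = 0.3 to 0.5 SD of connectivity in the hand calculation and 0.2 to 0.8 SD in the simulation. Eyes-closed share differing by 10 or 30 percentage points between the younger and older halves. True age effect zero. Two-sided test at 5%.

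**Step 1: approximation by halves.** False age difference = d × difference in share. Standard error of a difference between halves = 2/√N, which is 2/√360 = 0.105 SD and 2/√180 = 0.149 SD. False-positive rate = P(|Z + bias/SE| > 1.96).

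| N | Share difference | d | Bias (SD) | Bias/SE | False-positive rate |
|---|---|---|---|---|---|
| 360 | 10 points | 0.3 | 0.03 | 0.28 | 5.9% |
| 360 | 10 points | 0.5 | 0.05 | 0.47 | 7.6% |
| 360 | 30 points | 0.3 | 0.09 | 0.85 | 14% |
| 360 | 30 points | 0.5 | 0.15 | 1.42 | 30% |
| 180 | 30 points | 0.3 | 0.09 | 0.60 | 9% |
| 180 | 30 points | 0.5 | 0.15 | 1.01 | 17% |

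**Step 2: continuous age, as the plan specifies.** Simulated regressions (4,000 per setting) used connectivity = d × eyes closed + standard normal error, with the probability of closed eyes linear in age. A rise from 40% to 60% across the whole age range is a 10-point difference between halves; 30% to 70% is 20 points; 20% to 80% is 30 points. False-positive rates for age at N = 360, without adjustment:

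| Eyes-closed share, youngest to oldest | d = 0.2 | d = 0.5 | d = 0.8 |
|---|---|---|---|
| 50% throughout | 4.2% | 5.4% | 5.4% |
| 40% to 60% | 5.8% | 9.0% | 13.4% |
| 30% to 70% | 6.6% | 18.6% | 37.2% |
| 20% to 80% | 10.0% | 35.2% | 68.9% |

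At N = 180 the steepest gradient gives 7.5%, 21.2% and 41.8%, lower than at 360. At d = 0.5 the continuous analysis gives somewhat higher rates than the halves approximation (9.0% against 7.6%, and 35.2% against 30%).

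**Step 3: noise only.** With a 50:50 choice unrelated to age, residual variance rises by d²/4: 1%, 6% and 16% for d = 0.2, 0.5 and 0.8.

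**Step 4: after adjustment.** With eye state known for everyone and entered as a covariate, the false-positive rate is 4.2% to 5.3% at N = 360 and 4.7% to 5.6% at N = 180, and the mean spurious slope is about zero in every setting.

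**The case against.** The strongest reply is that both ingredients of the bias come from outside the document. The article does not say that eye state changes connectivity, or that children and adults choose differently. This stands, and it is why the result is conditional and shown as a range. The 30-point difference is a steep case: if the choice is linear in age, it means 60 points from youngest to oldest.

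A reader might infer that eye state goes unrecorded, so that a viewing effect could never be separated from maturation. The article does not support that. It is a condensed account, and scan-log fields and nuisance covariates are commonly left to the full protocol or analysis plan. What the article does state is the acquisition rule, and under that rule the condition differs between participants whether or not it is logged.

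A reader might also infer that the study's main conclusions are at risk. They are not shown to be. The hypotheses spelled out under Current study concern the extent of task activation, first-language aptitude, memory and white-matter connectivity; none depends on resting-state connectivity. The age regressions are described as exploratory. The problem is confined to one modality and what is derived from it.

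Finally, setting a single condition midway has its own risk. Collection began in 2019 and was projected to end in 2023. A switch would tie eye state to calendar time, and thus to age if the age mix of recruits drifts. This stands and shapes the fix.

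**Conclusion.** The concern holds in conditional form. The plan lets participants choose the scan condition and describes no analysis that accounts for the choice. If eye state affects connectivity, the cost is added noise; if the choice also varies with age, the age regressions on resting-state metrics are biased, along with what linked independent component analysis and the structural equation model take from them. The size depends wholly on the assumed state effect and age gradient. It is minor when both are small (5.8% at d = 0.2 with a rise from 40% to 60%), material when the gradient is steep, and absent when the choice is unrelated to age. A larger sample does not remove it. The point deserves action because the remedy is cheap, not because harm has been shown.

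**What to change.** - Record eye state at every remaining resting-state scan. For earlier scans, retrieve it from scan logs or, failing that, from participants, allowing for recall error that may itself differ between children and adults.
- Report the distribution of eye state by age. This shows directly whether bias is possible.
- Include eye state as a covariate in every resting-state model, and run a sensitivity analysis restricted to scans with known eye state.
- If one condition is set for the remaining scans, also adjust for scan period and check that the age mix is balanced before and after the change. Recording the state without changing the instruction avoids this complication.
- State as a limitation that scans of unknown state cannot be fully corrected. An unknown category mixes both conditions, so an age-related choice within it stays unadjusted.

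The cost is one recorded field, one covariate and one sensitivity analysis, plus the effort of tracing earlier scans. If the full protocol already records eye state, only the reporting and the models need to change.
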